### Inclusion criteria

≥8 years old and ≤ 18 years oldMeeting the diagnostic criteria for simple myopia, with −6.00 D ≤ refractive state ≤ −0.50 D, astigmatism ≤1.50 D, and having a normal vision after optically correctedAble to cooperate to complete the studyThe subjects and their guardians must both voluntarily sign an informed consent form

### Exclusion criteria

Those who have comorbidities or complications of other eye diseases, such as glaucoma, amblyopia, eye infections, etc.Those who have comorbidities of very severe heart, brain, liver, kidneys, hematopoietic system diseases and neuropsychiatric diseases, or systemic diseases that may affect the progression of myopiaThose who have had eye surgery or a history of eye traumaThose who have comorbidities of hearing abnormalitiesThose who are unable to cooperate with the study for personal or family reasonsThose who refuse to sign an informed consent form by himself/herself or any of his/her guardians

### Withdrawal criteria

Subjects have the right to withdraw from the study, as defined in the informed consent document, or to “drop out” if they do not explicitly withdraw from the study but are no longer undergoing training and testing. The reason for withdrawal should be understood as far as possible and recorded, for example, (1) perceiving lack of efficacy, (2) intolerance of certain adverse effects, (3) inability to continue the clinical study, and (4) or lost to follow-up without explanation. Case record forms for withdrawn subjects will be kept, and the results of the last trial will be considered final. The data on the clinical efficacy and adverse effects of the focused vision-guided meditation training will be fully analyzed.

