### Suspension criteria

The investigator will decide to terminate the study of a subject who has been enrolled in the study if the subject is unfit to proceed the study. For example, (1) the subject develops certain comorbidities and complications under study; (2) the subject is unfit to continue the study due to unexpected events or specific physio-pathological changes during the study. (3) The subject meets the criteria for cure in less than 30 days; the study may be discontinued early if the subject so desires.

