### Excluded cases

Those who with any of the following should be excluded:
Subjects with incomplete case information that affects the analysis of the trial results. For subjects, who missed 4 or more days in the first 7 days of treatment, or participated in daily training for less than 14 days. Patients with lost contact were followed up without corresponding prediction and correlation analysis. For research, more than half of the cases in which data was lost due to machine failure or forgetting to record.Subjects with poor compliance during the trial due to subjective or objective factors of their own or family members. Who shows obvious resistance, fall asleep, or play during training and continue to do so after being reminded by the researchers.Subjects who use other interventions for myopia outside the protocol: drug therapy, acupuncture, orthokeratology, etc.

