### Missing data

For primary outcome measurements monitored repeatedly, we used the final follow-up time point to calculate the missing rate. All evaluations, in particular the evaluation of the primary outcomes, will be made on the basis of all randomized patients, carry out a primary analysis of all observed data that are valid under a plausible assumption, regardless of whether or not they adhered to the treatment protocol or provided complete data sets.

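### The withdrawal and suspension rules have no status for a child who stops training but is still tested, which conflicts with the all-randomised, adherence-independent evaluation

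*Protocol article*

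**What the plan says.** **Leaving the study.** Under Withdrawal criteria there are two routes out: explicit withdrawal, and dropping out, which applies to children "if they do not explicitly withdraw from the study but are no longer undergoing training and testing". Records of withdrawn children are kept, and "the results of the last trial will be considered final". I take the last trial here to mean the last test result. Perceived lack of efficacy is the first reason listed.

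**Ending a child's study.** Suspension criteria states: "The investigator will decide to terminate the study of a subject who has been enrolled in the study", when the child is unfit to go on. For a child who meets the cure criteria in under 30 days, "the study may be discontinued early if the subject so desires". The Statistical analysis section defines cure as acuity of 5.0, so this trigger is on the primary outcome scale.

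**What is promised.** Under Missing data, all evaluations, the primary outcome in particular, "will be made on the basis of all randomized patients", "regardless of whether or not they adhered to the treatment protocol or provided complete data sets". The stated intention is to "carry out a primary analysis of all observed data that are valid under a plausible assumption".

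**When acuity is measured.** Intervention description, Primary observation indexes and Table 1 all schedule acuity at months 1, 2 and 3. None limits it to children who completed or are still in training. Table 1 also lists acuity at termination and at unscheduled visits.

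**The concern.** Stopping an intervention and leaving a trial are different events. An analysis of all randomised children irrespective of adherence needs outcomes from those who stopped. The withdrawal and suspension sections describe only the joint event: training and testing have both ceased, or the child's study has ended. A site following them could reasonably close a child's record when training ends, although the follow-up schedule implies that the child is still due for testing.

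The reasons for stopping are unlikely to be neutral. Children and those delivering the intervention know the allocation. One stated reason for leaving is perceived lack of benefit, and another route is having reached the acuity target. If readings after stopping are missing, a mixed model fills the gap by assuming that stopped children would have followed a course predictable from their earlier readings and from children who continued. That need not match what happened off training, so the result may not be the adherence-independent effect that was promised. Whether an early gain lasts to month 3 is one thing follow-up could show for children who reach cure early.

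**Working it through.** **1. The text side by side**

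| Section | What happens to a child who stops training | Later acuity readings |
|---|---|---|
| Withdrawal criteria | Dropped out if testing has ceased too | Last result is final |
| Suspension criteria | Study ended (unfit), or may be ended (cure before day 30) | Not provided for |
| Intervention description, Primary observation indexes, Table 1 | No distinction made | Months 1, 2 and 3 for everyone |
| Missing data | Evaluated regardless of adherence | All observed data used |

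The first two rows and the last two cannot all be applied to the same child. In Table 1, early quitting is marked on training days and at termination but not at months 1 to 3, so the table does not settle the matter.

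**2. The plan's own sample size**

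Inputs (Sample size): means 4.98 (SD 0.14) and 4.92 (SD 0.24), difference 0.06; two-sided alpha 0.05; power 0.90; ratio 2:1; dropout 20%.

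- Control n = (1.960 + 1.282)² × (0.24² + 0.14²/2) / 0.06² = 197, so 394 experimental.
- Dividing by 0.8 gives 247 + 493.

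The stated 190 + 380 is not reproduced. That is a separate matter and nothing below depends on it. I use the final 380 + 760 as given.

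**3. How many children**

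0.20 × 760 = 152 and 0.20 × 380 = 76, together 228 of 1140. This is an upper bound at the planned dropout rate, because the allowance also covers children lost to follow-up or unwilling to be measured.

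**4. Precision and power** (ignoring any centre effect)

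- SE with all children: √(0.14²/760 + 0.24²/380) = 0.0133.
- SE with 80% of them: √(0.14²/608 + 0.24²/304) = 0.0149, a ratio of 1.118, so an interval about 12% wider.
- Power (Welch) for 0.06 with 608 + 304: 98.0%.
- If all 1140 are measured and, by assumption, the 20% who stop show no between-arm difference, the effect is 0.06 × 0.8 = 0.048 and power is 94.9%. At 10% and 30% stopping, the powers among those remaining are 98.9% and 96.4%; with everyone measured they are 98.2% and 88.3%.

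Power is therefore not the argument. Measuring everyone may even lower it somewhat, because the effect then includes children who stopped.

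**5. Possible bias in a completer contrast** (all stopping rates and deficits are assumed)

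- 20% of the experimental arm stop and have none of the benefit: 0.20 × 0.06 = 0.012, or 20% of the planned effect.
- 25% stop in the experimental arm and 15% in control, and those who stop are one row (0.1) worse: (0.25 − 0.15) × 0.1 = 0.010, or 17%.
- The same rates with a two-row deficit: (0.25 − 0.15) × 0.2 = 0.020, or 33%.

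The sign reverses in the last two cases if more controls stop, or if those who stop are better than those who continue, as with stopping on cure. A mixed model using earlier readings would shift less, to the extent that those readings predict who stops.

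**6. Could the cure route be common?**

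Suppose the planning values describe acuity at the end of training and are normal; the protocol says neither. The share at or above 5.0 is then 1 − Φ((5.0 − 4.98)/0.14) = 44% in the experimental arm and 1 − Φ((5.0 − 4.92)/0.24) = 37% in control. How many would reach 5.0 before day 30, or choose to stop, is unknown. The route cannot be assumed rare.

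**The case against.** A reader might infer that children who stop training are removed from testing and that their month 1 to 3 readings are never collected. The documents do not support that. The definition of a drop-out describes children who have already ceased both activities; it does not order testing to stop when training stops. A child who stops training but still attends tests is not a drop-out under it. The month 1 to 3 schedule has no adherence restriction. The abstract says that no intervention is given in follow-up, so being off training cannot by itself end follow-up testing. Ending the study on cure is the child's option, not automatic. The Missing data section also expects incomplete data. All of this stands.

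A second objection is that collection of outcomes after a child stops is detail which an article leaves to the full protocol. Silence alone would indeed be no finding. But the article does not merely stay silent. It states that a withdrawn child's last result is final and that a child's study can be ended, and these rules conflict with its own analysis principle and schedule.

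A third is that the neighbouring rules are the real trouble: using the last result as final, and excluding children who "missed 4 or more days in the first 7 days of treatment, or participated in daily training for less than 14 days". The exclusions may only define the per-protocol set; the text does not say. Correcting how data are used would still not secure readings that were not taken.

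Finally, the bias figures concern a completer contrast with assumed inputs, whereas the plan specifies a linear mixed model. That is right, and they are illustrations only.

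**Conclusion.** The point holds as an unresolved conflict in the text. The withdrawal and suspension rules allow month 1 to 3 acuity to go unmeasured for reasons related to outcome or perceived benefit, while the Missing data section and the visit schedule imply that it is measured and used. The protocol does not establish that these readings will be lost.

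At most 228 of 1140 children are involved if dropout is as planned, and not all of them could be recovered. The consequence is possible bias and an unclear target of estimation, not inadequate power. The size and direction of the bias are unknown; the 0.010 to 0.020 range rests on assumed stopping rates and deficits and would be smaller under the planned model. This is a cheap improvement to make before children begin to stop, not a flaw that invalidates the design.

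**What to change.** In Withdrawal criteria and Suspension criteria:

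- Separate two statuses: stopped training, and withdrew from the study.
- State that every randomised child who has not withdrawn consent or assent for measurement keeps the scheduled acuity tests through month 3, whatever the reason training stopped.
- Record the date and reason for stopping.
- Analyse these readings under the assigned arm in the all-randomised mixed model, and reconcile the rule that makes the last result final with this.

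The criteria for stopping training do not change.

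The cost is protocol wording and a few more acuity tests at visits already scheduled. The protocol places training in schools but does not say where follow-up acuity is measured, so the practical burden should be confirmed. The estimate may be somewhat less favourable, because it will include children who stopped.

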### Suspension criteria

The investigator will decide to terminate the study of a subject who has been enrolled in the study if the subject is unfit to proceed the study. For example, (1) the subject develops certain comorbidities and complications under study; (2) the subject is unfit to continue the study due to unexpected events or specific physio-pathological changes during the study. (3) The subject meets the criteria for cure in less than 30 days; the study may be discontinued early if the subject so desires.

### Excluded cases

Those who with any of the following should be excluded:
Subjects with incomplete case information that affects the analysis of the trial results. For subjects, who missed 4 or more days in the first 7 days of treatment, or participated in daily training for less than 14 days. Patients with lost contact were followed up without corresponding prediction and correlation analysis. For research, more than half of the cases in which data was lost due to machine failure or forgetting to record.Subjects with poor compliance during the trial due to subjective or objective factors of their own or family members. Who shows obvious resistance, fall asleep, or play during training and continue to do so after being reminded by the researchers.Subjects who use other interventions for myopia outside the protocol: drug therapy, acupuncture, orthokeratology, etc.

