### Statistical analysis

Multiple factors that affect this trial will be taken into consideration. Participates from different areas with similar school level will be stratified. A stratified randomizing method will also be adopted according to region, age, gender, etc. Similar stratified groups will be compared; the experimental and the control groups are launched within the same school.

We will use a linear mixed model to analyze incorporating repeated measures. Firstly, visual acuity is independent among subjects and is the primary indicator of observation. Otherwise, it will be measured at the end of each training session and followed up for 3 months. That is important to model the correlation of these repeated measurements.

Statistical analysis using SPSS 20.0 will be performed, and data management software will be used to construct the database. Dedicated staff will be assigned to oversee the management of electronic data, and a clinical research team will be deployed for data entry, validation, reporting, and answering questions. Normally distributed variables will be expressed as their mean and standard deviation (SD), and frequency (percentage) for categorical variables. Baseline characteristics between the intervention and control groups will be compared by performing a two-sample *t*-test and Wilcoxon rank-sum test for continuous variables with and without normal distribution, respectively. All *P*-values are 2-sided and considered statistically significant when less than 0.05.

Primary and secondary observation indexes will be analyzed by the superiority test depending on the treatment, using Per Protocol Set (PPS) and Full Analysis Set (FAS) datasets. The indices of safety evaluation will be analyzed using the Save Set (SS) dataset.

According to the ophthalmic disease efficacy evaluation standard in the Guidelines for Clinical Research of Traditional Chinese Medicine New Drugs:
Cure: visual acuity to normal (5.0)Significant effect: visual acuity improved by 4 lines or more with a visual chartImprovement: visual acuity improved by 2 lines or moreIneffective: visual acuity improved by less than 2 rows or decrease

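### Exclusions made after randomisation are not confined to the per-protocol set, conflict with the all-randomised rule, and leave open which set governs the efficacy claim and phase 2

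*Protocol article*

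**What the plan says.** Excluded cases opens with an unqualified instruction: "Those who with any of the following should be excluded". The grounds listed are:

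- incomplete records: "Subjects with incomplete case information that affects the analysis of the trial results";
- low attendance: children "who missed 4 or more days in the first 7 days of treatment, or participated in daily training for less than 14 days";
- poor compliance: "Subjects with poor compliance during the trial due to subjective or objective factors of their own or family members", which extends to a child "Who shows obvious resistance, fall asleep, or play during training and continue to do so after being reminded by the researchers";
- use of other myopia treatment outside the protocol.

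Missing data says that all evaluations, the primary outcome in particular, are "made on the basis of all randomized patients", whether or not the child adhered or supplied complete data. It asks for a primary analysis of all observed data.

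Statistical analysis applies the superiority test to the primary and secondary indexes "using Per Protocol Set (PPS) and Full Analysis Set (FAS) datasets". It does not say which of the two leads.

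Two further sections bear on the point. Suspension criteria allows an early stop: "The subject meets the criteria for cure in less than 30 days; the study may be discontinued early if the subject so desires". Second phase makes the start of phase 2 depend on the phase 1 comparison, without naming an analysis set.

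**The concern.** Every ground under Excluded cases becomes known only after allocation; eligibility at entry is dealt with separately under Exclusion criteria. Removing children on such grounds means that the groups compared are no longer the groups randomised.

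Part of the judgement also falls to people who know the allocation. Implementation says that executors and subjects are not blinded, and Quality control gives each arm its own teachers in its own classroom. Persistent resistance or play would therefore be judged by unblinded staff, and not necessarily by the same standard in both arms. Withdrawal criteria lists a perceived lack of efficacy among the reasons for leaving, so stopping can be related to outcome.

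At stake are the primary comparison and the decision on phase 2. If the two sets disagree, the protocol does not say which result counts.

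**Working it through.** The protocol gives no figure on this point, so there is none to reproduce. The finding rests on the text.

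**1. The two rules side by side.**

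| Ground | Excluded cases | Missing data |
|---|---|---|
| Incomplete records | Exclude | Keep, whatever the completeness |
| Low attendance | Exclude | Keep, whatever the adherence |
| Poor compliance or resistance | Exclude | Keep, whatever the adherence |
| Outside myopia treatment | Exclude | Keep, as a randomised child and a departure from protocol |

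Adherence and completeness are what the first rule excludes on and what the second says must not matter.

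**2. Does Statistical analysis reconcile them?** No. It names PPS and FAS but does not tie the PPS to Excluded cases or the FAS to Missing data. Read literally, a rule covering all evaluations also leaves no room for a PPS analysis.

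**3. Direction of the bias.** It is not fixed:

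- Dropping poor attenders with worse acuity from the experimental arm would enlarge the difference.
- Dropping early-cured children from the experimental arm would shrink it.
- Dropping dissatisfied controls who turn to other treatment and see poorly would raise the control mean and shrink it.

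**4. Early cure.** Statistical analysis sets cure at 5.0. A child who reaches it and stops before completing 14 days, as Suspension criteria permits, could meet the attendance exclusion, which has no exemption for this. The Sample size figures suggest that cure need not be rare. Assuming normality:

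- experimental arm: (5.0 − 4.98)/0.14 = 0.14, so about 44% at or above 5.0;
- control arm: (5.0 − 4.92)/0.24 = 0.33, so about 37%.

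How many would get there before day 14 is unknown.

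**5. Illustration of having no stated lead set.** Assume that success could be declared on either set at two-sided 0.05, that there is no true effect, and that exclusion is unrelated to outcome. The two test statistics are then approximately bivariate normal with correlation √(share retained). The type I error is P(|Z₁| > 1.96 or |Z₂| > 1.96).

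| Share retained in PPS | Type I error |
|---|---|
| 95% | 6.0% |
| 90% | 6.5% |
| 80% | 7.1% |
| 70% | 7.6% |

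The retained shares are assumptions. Exclusions related to outcome would add bias on top, of unknown size and sign.

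**The case against.** The best defence is that Excluded cases is simply an unlabelled PPS definition. Two sets make sense only if some exclusions apply to one and not the other, and no other text could define the PPS. Withdrawal criteria also points away from deletion: forms are kept and the last result stands. Formal definitions of the sets are often left to the full protocol or the SAP.

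Much of this is reasonable, and it is probably what was meant. But the protocol does not say so. The exclusion is unconditional, and the conflict lies between two published rules. An SAP author would have to depart from one of them. Missing definitions are not the complaint here.

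Three stronger readings are tempting and are not supported:

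- **That no primary population exists.** Missing data does call for a primary analysis of all observed data on all randomised patients. What is missing is the link from that to the labels PPS and FAS. A claim resting on PPS alone would contradict that section.
- **That sleep during eyes-closed sessions in a darkened room makes exclusion fall mainly on the meditation arm.** The darkened session belongs to the first audio set, used on days 1 and 8 only. The daily sessions are eye exercises and character-card work, and the behaviour must persist after a reminder.
- **That the exclusions would flatter meditation by a known amount.** One could multiply an assumed net excluded share by an assumed acuity gap: 0.10 × 0.10 = 0.01, up to 0.20 × 0.20 = 0.04. The comparison would be the smallest significant difference at 608 and 304 children, 1.96 × √(0.14²/608 + 0.24²/304) = 1.96 × 0.01489 = 0.029. Neither input is in the protocol, only the upper part of the range passes 0.029, and step 3 shows that the sign is open.

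**Conclusion.** The concern holds as a conflict between stated rules. Excluded cases and Missing data cannot both be followed, and Statistical analysis does not say which set governs the efficacy claim or the phase 2 decision. The exclusions arise after randomisation and are partly judged by unblinded staff, so applying them to the main comparison could bias it either way. The protocol does not allow the size of that bias to be derived. The 6.0% to 7.6% type I error illustrates only the unstated hierarchy, under the assumptions given, and is not an estimate for this trial. The conflict itself needs no assumption, and it should be settled before any outcome comparison is seen.

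**What to change.** 1. Label Excluded cases as the definition of the PPS and of nothing else.
2. State that the population described under Missing data is the FAS: every randomised child in the allocated arm, with all observed acuity kept whatever the adherence, behaviour in training or outside treatment. Say that children who stop early after cure remain in it.
3. Name the FAS as the single primary analysis for both the efficacy claim and the phase 2 decision, with the PPS supportive.
4. Limit the Missing data rule on all evaluations to the FAS analyses, so that it no longer rules out the PPS.

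This follows the principle already stated under Missing data and changes wording only. The cost is that the FAS estimate may be less favourable than the PPS one. To gauge it, suppose a share f of children would be excluded, are kept, and show no effect, so that the planned difference of 0.06 becomes 0.06 × (1 − f). Power below is from a Welch t-test with SDs 0.14 and 0.24, two-sided 0.05, all children observed. The second power column assumes that the doubling for centre effect is wholly used up.

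| f | Difference | 760 + 380, no clustering | Effective 380 + 190 |
|---|---|---|---|
| 0% | 0.060 | 0.99 | 0.89 |
| 10% | 0.054 | 0.98 | 0.81 |
| 20% | 0.048 | 0.95 | 0.72 |
| 30% | 0.042 | 0.88 | 0.60 |

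The loss is small if clustering is slight, and more noticeable if it takes up the whole reserve.

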### Recruitment

In this trial, 1140 primary and secondary school students with simple myopia will be recruited from 27 schools in Sichuan and Hunan provinces or other cities with relatively uniform schooling conditions. School factors will be taken into consideration. We will choose participates from different areas with similar teaching level as the subjects. In the meanwhile, a comparison of the experimental group and the control group is launched within the same school in order to reduce the variance.

The main points for the diagnosis of simple myopia in China’s “Myopia Prevention and Treatment Guidelines” [19] will be used as a reference standard for recruitment: near visual acuity is normal; distance visual acuity is less than 1.0 (5.0 by the mucosal method); there are no pathological changes in the fundus; the progression is slow; vision can be corrected to normal with appropriate lenses, while other visual function indicators are mostly normal; and the subject recruited meet the quantitative criteria for myopia according to the “White Paper on Myopia Prevention and Control” of the International Myopia Institute (IMI) [20]: myopia diopter ≤ −0.50D.

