### Primary observation indexes

Visual acuity training aims to improve naked eye visual acuity, which affects life and work and will be used as the main observation index. Visual acuity tests were performed before and after each training session for the first 7 days, once a week after 7 days of training and at the first, second, and third months of follow-up, respectively.

The specification for visual acuity testing is based on the “Expert Consensus on Workflow of Myopia Screening in Children and Adolescents (2019)” [21]. The international standard logarithmic visual acuity chart is adopted. During the measurement, the subjects stand 5 m away from the visual acuity chart and cover the contralateral eyes without squinting and oppression. The covered eyes are examined first in the right eye and then in the left eye. If the inspector can identify half or more of the visual markers, check them line by line from top to bottom and ask the subjects to say or gesture the direction of the gap of the visual markers within 5 s. The last line of the visual markers that is correct will be the testee’s vision of that eye. For example, if row 4.8 cannot be identified, check upward until half or more of the rows can be identified.

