## Statistical analysis

### Sample size

The sample size will be estimated based on our early observations [23]. The treatment group was 4.98 ± 0.14, and the control group was 4.92 ± 0.24. Under 20% dropout rate, with the two-tailed *α* = 0.05 and *β* = 0.1 (test efficacy of 0.9), experimental group: control group = 2:1, PASS 15.0 software calculation shows 380 in the experimental group and 190 in the control group. Due to the possible center effect, the final sample size is suggested to be twice expanded. Thus, it is finally confirmed there will be 1140 cases in total, with 760 cases in the experimental group and 380 cases in the control group.

Statisticians suggest that we appropriately expand the sample size to reduce the impact of the central effect on the final results.

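### A child permitted to stop early on reaching cure can then be excluded for too few training days, so per-protocol membership partly depends on the primary outcome

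*Protocol article*

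**What the plan says.** Four parts of the Protocol article bear on this.

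- **Suspension criteria, item 3** permits an early exit: "The subject meets the criteria for cure in less than 30 days; the study may be discontinued early if the subject so desires".
- **Statistical analysis** defines the criterion: "Cure: visual acuity to normal (5.0"). Recruitment admits children whose "distance visual acuity is less than 1.0" (5.0 on the logarithmic scale), so cure means crossing the entry threshold.
- **Excluded cases** says that subjects "who missed 4 or more days in the first 7 days of treatment", "or participated in daily training for less than 14 days" should be excluded. It makes no exception for a stop on cure and does not name the analysis set.
- **Statistical analysis** plans the superiority tests of the primary and secondary indexes "using Per Protocol Set (PPS) and Full Analysis Set (FAS) datasets". **Missing data** bases all evaluations, the primary outcome above all, on everyone randomized, whatever their adherence or completeness of data.

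Withdrawal criteria adds that a withdrawn subject's forms are kept and the last result stands. It does not say whether a child who stops on cure counts as withdrawn, or whether this overrides Excluded cases.

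**The concern.** One section grants an exit that the next section penalizes. A child who reads 5.0 on day 9 and leaves as allowed is a cure under the efficacy standard and also an excluded case. A child who leaves on cure on day 18, having attended at least 14 days, is not caught by the training-day rule. Whether a cured child stays in the set therefore depends on when the best outcome was reached.

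The situation can arise. Under Primary observation indexes, "Visual acuity tests were performed before and after each training session for the first 7 days", so a reading of 5.0 can be recorded well before day 14. The efficacy standard mentions no confirmatory reading.

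At stake is the per-protocol comparison. A minimum-exposure rule is ordinary when exposure is unrelated to outcome. Here a good outcome can be the reason for the short exposure, so the rule selects on the primary endpoint. If the two arms differ in how often this happens, or in how far their cured children lie above the arm mean, the between-arm difference shifts.

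**Working it through.** **Step 1: the rules side by side, for a child who reaches 5.0 and chooses to stop.**

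| Stops after | First-week rule (4 or more of 7 days missed) | Under-14-days rule | Result as written |
|---|---|---|---|
| Day 3 | met (days 4 to 7 missed) | met | excluded |
| Day 9 | not met if attending until then | met | excluded |
| Day 18, at least 14 days attended | not met if attending until then | not met | not caught by these rules |

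All three exits are allowed by Suspension criteria item 3, and all three children meet the cure definition.

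**Step 2: which analysis is affected.** If the exclusions applied to the full analysis set, they would contradict Missing data. The consistent reading is that they define the per-protocol set. This is an inference.

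**Step 3: possible size.** The documents give no rate of early stops on cure, so this is an illustration.

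Inputs, from Sample size: "The treatment group was 4.98 ± 0.14, and the control group was 4.92 ± 0.24". The plan's own difference is 4.98 − 4.92 = 0.06.

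Assumptions: acuity is normal in each arm with these means and SDs; cured means at or above 5.0; a share f of cured children stops before 14 training days and is removed.

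Formulas, with z = (5.0 − mean)/SD:
- share at or above 5.0: p = 1 − Φ(z)
- mean of those children: m = mean + SD × φ(z)/p
- arm mean after removal: (mean − f·p·m)/(1 − f·p)

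Trained: z = 0.02/0.14 = 0.143, p = 0.443, m = 5.105.
Control: z = 0.08/0.24 = 0.333, p = 0.369, m = 5.165.

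Worked case, f = 5% in both arms:
- Trained: f·p = 0.022, arm mean 4.977.
- Control: f·p = 0.018, arm mean 4.915.
- Difference 0.062.
- Children removed: 760 × 0.443 × 0.05 ≈ 17 and 380 × 0.369 × 0.05 ≈ 7.

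| Removed share of cured, trained / control | Per-protocol difference |
|---|---|
| 0% / 0% | 0.060 |
| 5% / 5% | 0.062 |
| 10% / 10% | 0.064 |
| 20% / 20% | 0.067 |
| 20% / 5% | 0.053 |
| 20% / 0% | 0.048 |
| 5% / 20% | 0.077 |
| 0% / 20% | 0.080 |

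**Reading the table.** Equal removal raises the difference because cured controls lie further above their arm mean (5.165 − 4.92 = 0.245) than cured trained children do (5.105 − 4.98 = 0.125). Removal concentrated in the trained arm lowers it.

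**The case against.** The strongest reply is that the main analysis is protected and the rest is detail for the analysis plan. Much of this stands. Missing data keeps everyone randomized in the primary evaluation, and Withdrawal criteria preserves the last result of withdrawn subjects. A reader might infer that cured children are discarded from the trial and their readings lost. The documents support at most a loss from the per-protocol set, and even that link is inferred.

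The reply does not dispose of the point. Detailed per-protocol rules are commonly left to an analysis plan, but here the document states both rules, and following both produces the selection.

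Three further limits stand.

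- **Fastest responders.** A reader might infer that the best responders are removed as poor attenders. Entry requires only acuity below 5.0, so some early cures will be children who started just under the line. The protocol does not call them poor attenders either: the training-day rules sit with incomplete case information, and poor compliance is a separate item. Nor does it promise that a day-18 leaver is kept; that child might be excluded on other grounds.
- **A large bias.** Removing 50% of cured trained children and 10% of cured controls would cut the difference to 0.034. That takes 0.5 × 0.443 = 22% of the trained arm by this one route, against 20% assumed for all dropout. Nothing in the documents supports such rates, or shows that rates differ by arm.
- **The model.** Sample size gives neither the time point of its means nor whether the unit is the eye or the child. The illustration also gives early leavers the average of all children at or above 5.0, although they may stop at about 5.0.

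**Conclusion.** The point holds for the per-protocol set. Suspension criteria and Excluded cases, applied together as written, make exclusion depend on the primary outcome for children who reach 5.0, choose to stop, and do so before 14 training days or early in the first week. If Missing data governs, the all-randomized analysis is unaffected.

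The size cannot be taken from the documents. Under the stated assumptions the shift is only 0.002 to 0.004 when 5% or 10% of cured children are removed in both arms. It reaches −0.012 or +0.020 when 20% are removed in the trained arm only or the control arm only. The direction cannot be known in advance. What is certain is the clash between the rules; a material bias is possible but not shown. The clash is worth correcting because the correction is cheap.

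**What to change.** Reconcile Withdrawal criteria, Suspension criteria, Excluded cases and Missing data. Specifically:

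1. State in Excluded cases that its exclusions define the per-protocol set only.
2. State there that a child who stops under Suspension criteria item 3 is not counted as having too few training days and stays in the per-protocol set.
3. Record the date and reason of each such stop.
4. Where the family agrees, keep collecting the acuity readings already scheduled, through month 3 of follow-up.

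Whether and when training may stop is for the sponsor to decide; no change to that rule is proposed here.

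The cost is a few sentences of protocol text, some readings on children who have finished training, and a per-protocol set that includes some short courses. In the 5%/5% illustration this concerns about 17 + 7 = 24 children, or 24 × 3 = 72 monthly follow-up readings plus any remaining weekly tests, all already in the schedule. Higher rates of early stopping would raise this in proportion.
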